##### Cognitive Theory of Mind Tasks

The cognitive theory of mind is evaluated using the concept of false belief, which is accepted as a reliable indicator. Four stories of false beliefs, based on published tasks (31–34), are told to children using illustrations. Each aims to evaluate, using questions regarding the story, the children's ability to understand that a character may misconceive reality or understand what another character believes.

##### Affective Theory of Mind Tasks

Two tasks evaluating the affective theory of mind have been proposed in the form of stories told to children. The first, called an emotional perspective task (35) (based on the work of Harwood and Farrar, 2006), evaluates children's ability to understand the emotional state (joy, anger, fear, or sadness) of another even when the other person experiences an emotion that is different from their own. The second, called the emotion inference task (36), measures children's ability to deduce (1) the emotion experienced by a character (joy, anger, fear, or sadness) from his false belief (he is sad because his belief is false) but also (2) the emotion experienced by a character who is a victim of a faux pas (37).

#### Clinical Data Collected From Parents

##### The State-Trait Anxiety Inventory Scale Version Y

The State-Trait Anxiety Inventory (STAI) (38) is designed to evaluate anxiety-trait and anxiety-state using 20 questions that only concern the psychological and non-somatic aspects of anxiety. Version Y was developed to eliminate questions that are more related to depression. The STAI is used both in practice and in clinical research. It includes separate scales for evaluating the state (STAI Form Y-A) and the trait (STAI Form Y-B). Each of the scales includes 20 propositions; the S scale to evaluate what subjects are feeling at the time, and the T scale to capture what subjects are generally feeling. The STAI is intended for self-administration, and can be completed individually or in groups. The handover time is approximately 10 min to complete both scales. Each response to a proposition in the questionnaire corresponds to a score of 1 to 4 (1 indicating the lowest level of anxiety and 4 indicating the highest level).

##### The Beck Depression Inventory Scale, 2nd Version

The Beck Depression Inventory 2nd version (BDI-II) scale (39) has three objectives; to screen for depression, to evaluate the severity of previously diagnosed depression, and to aid monitoring of the efficacy of therapeutic interventions. The tool provides a quantitative estimate of the intensity of depressive feelings. It includes 21 questions of symptoms and attitudes that describe a specific behavioral manifestation of depression, graduating from 0 to 3 using a series of for statements reflecting the severity of the symptoms. This scale was translated and validated to French by Bourque and Beaudette in 1982 (40).

##### Perceived Social Support Questionnaire-6

The Perceived Social Support Questionnaire (PSSQ) (41) is a self-evaluation scale that evaluates the availability of and satisfaction with perceived social support. The authors were inspired by Bowlby's attachment theory, associating the notion of social support with basic needs; the need for closeness to the mother, and the need for a meaningful privileged relationship with others. This scale therefore makes it possible to evaluate the type of support received, the sources of this support, the number of people who provide it (or availability), and the perceived quality (or satisfaction). The four main forms of social support are represented by the four questions of the scale; esteem support (comfort, listening in difficult times), material or financial support (direct assistance when necessary), informational support (advice or suggestions from others), and emotional support (reassurance, confidence building). For each type of support, the questionnaire makes it possible to know how many people provide it, who these people are (family, friends, colleagues, specialists, etc.), and whether the subject is satisfied with this support. Two scores are obtained for each subject; availability (number of people who participated in the support) and perceived satisfaction (”quality“) of the support. This tool also provides information regarding the nature of the person's perceived social support. This is a self-administered questionnaire completed by the subject (requiring 4–6 min to complete). Regarding the four questions related to the availability of social support, the subject must indicate the number of people they can rely on in these four categories; family, friends/peers, colleagues, and health professionals. For the satisfaction questions, the subjects are required to rate their level of satisfaction on a five-point Likert scale. The total availability score is obtained by summing the responses indicated by the subject on the ”how many“ questions. To calculate the total satisfaction score for support, the responses (from 1 to 5) indicated by the subject on the satisfaction questions are summed. The questionnaire was translated to French by Bruchon-Schweitzer and Quintard (42).

##### Modified Perinatal Post-traumatic Stress Disorder Questionnaire

This is a 14-question self-administered questionnaire specially adapted for the parents of children at high perinatal risk and used to evaluate the presence of traumatic elements related to childbirth (43). Its construction refers to the DSM-IV criteria for post-traumatic stress disorder (intrusion, avoidance, and hypervigilance). The questions are retrospective, and the mother must answer questions regarding symptoms that appeared at birth and persisted for >1 month. We will use the version modified in 2006, with the same questions as in the original version (44), but with the possibility of answering on a four-point Likert scale, from 0 (not at all) to 4 (often for >1 month). The Perinatal Post-Traumatic Stress Disorder Questionnaire is specific to the birth of a baby at risk, and can be expected to be more appropriate than other scales for this particular event. This tool has been translated into French and validated by Pierrehumbert's team (45).

##### Brief Form of the Parental Stress Index

The Parental Stress Index (46) is a measurement tool used to detect difficulties in parent-child dyad interactions. Parental stress is defined as a state of psychological discomfort related to the specific area of the child's upbringing, i.e.,the stress of the parent at the time of raising the child. The questionnaire used to measure this stress consists of 101 questions divided into two categories of stressors; those associated with the child's domain and those associated with the parent's domain. The parent's responses are provided on a five-point Likert scale that represents the respondent's level of agreement or disagreement with each of the stated propositions.

The short form is comprised of 36 questions derived from the long form (101 questions). For the short form, the results are organized into three sub-scales (parental distress, dysfunction in parent-child interaction, and child difficulties) in addition to providing a total score for the stress generated by the parent-child relationship. The higher the value identified, the higher the level of stress.

#### Socio-Demographic Data

##### Clinical Data of Pregnancy

Medical assistance for procreation, risk of preterm delivery, hospitalization, pregnancy-related pathologies, intercurrent events during pregnancy, and type of delivery (normal, or scheduled or emergency cesarean section).

##### For the Child

Age, sex, school level, birth in weeks of amenorrhea, gestational weight, rank in siblings, childcare, breastfeeding, medical/surgical history, APGAR and Perinatal Risk Inventory (PRI) score, specific follow-up (speech therapy, psychomotricity, orthoptics, psychological follow-up), and child psychiatry or neuropediatric monitoring.

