### Participants and Procedure for Recruitment

The subjects will be children born at the maternity ward of the CHU de Reims, France (Reims University Hospital). Information will be given by telephone to caretakers by a clinical research assistant. Once the parent or legal guardian of the children consent to participate in the study, written informed consent will be obtained from the parent or legal guardian of the children. Both the child and the parents or legal guardian must provide their consent for the child's participation in the study.

A total of 28 children born prematurely at the Reims University Hospital, aged 7-10 years (“preterm”), and 28 children born full-term at the Reims University Hospital, aged 7-10 years (“control”), will be included. The “preterm” and “control” groups will be matched for sex and age (± 3 months).

The inclusion criteria are as follows:

“Preterm” children: (1) Children born prematurely (before 37 weeks), making a clear distinction between high and medium preterm infants, (2) aged 7–10 years at the time of inclusion, and (3) enrolled in a non-specialized primary school;

“Control” (full-term) children: (1) Children born at ≥37 weeks, (2) aged 7–10 years, and (3) enrolled in primary school.

“Preterm” and “Control” children: (1) Children and parents affiliated with a social security system, and (2) holders of parental authority will have signed an informed consent form.

The exclusion criteria for the “preterm” and “control” children are as follows:

*Related to the child:* (1) Children with intrauterine growth restriction, (2) multi-pregnancy children, (3) children with organic malformation, (4) children with genetic abnormalities, (5) children with neuro-motor pathology, (6) children with overall developmental delay (IQ of <80), and (7) children refusing to participate in the study.

*Related to the parents:* (1) Minor parents, (2) parents with a proven intellectual deficit, (3) parents with acute or chronic psychotic disorders, (4) parents with difficulties in understanding and speaking the French language, (5) parents under a protective regime (guardianship or curatorship), and (6) parents refusing to participate in the study.

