##### For the Parents

Age, marital status, level of education, occupation, number of children, use of psychoactive substances (alcohol, tobacco, cannabis, etc.), personal and family psychiatric history, and psychiatric/psychological follow-up (psychiatric hospitalization, psychotropic treatments), neurological history (follow-up, treatment).

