#### Sample Size

Because of lack of literature, sample size calculation could not be performed on association between theories of mind and prematurity. Because of link between verbal skills and TOM has been shown in several studies that highlighted the impact of verbal skills on TOM task performance (47, 48), the calculation of the number of subjects required was performed for association between prematurity and WISC VCI with the following hypotheses: an average VCI score for “control” patients of 103.2 ± 12.6 (49) and an average VCI score for “preterm” patients of 92. With an alpha risk of 5%, a power of 90%, and a bilateral test, the number of patients required was 28 per group (NQuery software version 4.0).

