#### Statistical Analysis

Descriptive analysis will be performed. Quantitative variables will be expressed as the mean± standard deviation or median (range) and qualitative variables as number (percentage).

Factors associated with development of the affective and cognitive theories of mind separately, notably groups (“preterm”/“full-term”) and parental anxiety, will be studied using univariate analysis (Wilcoxon tests for qualitative variables and Spearman's correlation tests for quantitative variables) and multivariate analysis (linear regression with variables with a *p* < 0.10 by univariate analysis included).

The association between executive functions, evaluated using NEPSY-II, and the development of theories of mind will be studied using univariate analysis (Wilcoxon tests for qualitative variables and Spearman's correlation tests for quantitative variables) and multivariate analysis (linear regression with variables with a *p* < 0.10 by univariate analysis included).

The association between the executive functions, evaluated using the TEA-CH, and the development of the theories of mind will be studied using univariate analysis (Wilcoxon tests for qualitative variables and Spearman's correlation tests for quantitative variables) and multivariate analysis (linear regression with variables with a *p* < 0.10 by univariate analysis included).

A *p* < 0.05 will be considered significant. Statistical analysis will be performed using SAS (Version 9.4, SAS Institute, Cary, NC, USA).

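### The p < 0.10 entry rule lets child follow-up care into the regression beside group, where it can distort the adjusted preterm–control difference

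*Protocol article*

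**What the plan says.** The Main Objective is a comparison of affective and cognitive theory of mind between preterm and full-term children. The Statistical Analysis section gives that comparison no model of its own. It studies "Factors associated with development of the affective and cognitive theories of mind separately, notably groups (“preterm”/“full-term”) and parental anxiety", first by univariate tests (Wilcoxon or Spearman) and then by "multivariate analysis (linear regression with variables with a *p* < 0.10 by univariate analysis included". The same entry rule is repeated for the NEPSY-II and TEA-CH analyses. Group and parental anxiety are named as examples, so the list of factors is open. Group is not said to stay in the model whatever its p-value, and no class of variable is ruled out.

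Under Socio-Demographic Data, *For the Child*, the recorded items end with "specific follow-up (speech therapy, psychomotricity, orthoptics, psychological follow-up), and child psychiatry or neuropediatric monitoring". The article does not name these items as candidate covariates, does not exclude them, and does not say why such care is given. The Sample Size section adds that earlier studies "highlighted the impact of verbal skills on TOM task performance".

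**The concern.** Follow-up such as speech therapy or psychological care starts after birth. It may be given because a child has difficulties of the kind that the Hypotheses section expects in preterm children. It would then be a consequence of the deficit rather than a confounder, and holding it constant would remove part of the difference that the study sets out to measure. A univariate screen does not protect against this: the more closely follow-up tracks the outcome, the more surely it passes p < 0.10. The adjusted group coefficient, which readers often take as the more rigorous one, could then understate the difference or lose significance because of how the model was built.

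**Working it through.** **1. The plan's own figure.** Sample Size inputs: control mean 103.2, SD 12.6, preterm mean 92, two-sided alpha 5%, power 90%. The difference is 103.2 − 92 = 11.2, or 11.2/12.6 = 0.889 SD. The normal approximation gives n = 2(1.960 + 1.282)²/0.889² = 26.6, so 27 per group. With the noncentral t distribution, power is 0.893 at 27 and 0.904 at 28, so the stated 28 per group is reproduced. This effect is for the verbal index; the article gives none for theory of mind.

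**2. Why adjustment moves the coefficient.** In least squares, b(unadjusted) = b(adjusted) + γ·δ. Here b is preterm minus control, γ is the coefficient of follow-up given group, and δ is the preterm minus control proportion in follow-up. With δ > 0, the adjusted difference shrinks if followed children score lower than others in their own group (γ < 0) and grows if they score higher (γ > 0).

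**3. Simulation at the plan's effect.** 28 per group, true difference 0.889 SD, 4000 trials per setting, one binary follow-up variable. It entered the regression only if its Wilcoxon p was below 0.10. Group was always kept, which is kinder than the stated rule. The probability of follow-up was logit P = a − b·(score before any benefit) + c·(preterm), with (a, b, c) = (−1, 0, 0) unrelated, (−1, 0.5, 0) weak, (−1.5, 1, 0) moderate, (−2, 2, 0) strong and (−2, 0, 2) preterm status only. All of these values are assumptions.

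| Follow-up depends on | Benefit of care (SD) | Followed, preterm / control | Passes screen | Difference without → with the rule | Power without → with the rule |
|---|---|---|---|---|---|
| nothing | 0 | 27% / 27% | 10% | 0.885 → 0.881 | 0.900 → 0.898 |
| deficit, weak | 0 | 37% / 28% | 55% | 0.897 → 0.852 | 0.908 → 0.887 |
| deficit, moderate | 0 | 38% / 22% | 94% | 0.897 → 0.766 | 0.910 → 0.839 |
| deficit, strong | 0 | 46% / 22% | 100% | 0.887 → 0.587 | 0.908 → 0.711 |
| deficit, moderate | 0.5 | 37% / 22% | 47% | 0.810 → 0.763 | 0.884 → 0.842 |
| deficit, strong | 0.5 | 47% / 22% | 97% | 0.768 → 0.590 | 0.891 → 0.718 |
| preterm status only | 0 | 50% / 12% | 35% | 0.889 → 0.848 | 0.903 → 0.846 |
| preterm status only | 0.5 | 50% / 12% | 11% | 0.700 → 0.725 | 0.706 → 0.736 |
| preterm status only | 1.0 | 50% / 12% | 56% | 0.515 → 0.754 | 0.413 → 0.708 |

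For the three deficit-driven settings without benefit, the loss against 0.889 is 1 − 0.852/0.889 = 4%, 1 − 0.766/0.889 = 14% and 1 − 0.587/0.889 = 34%. Step 2 explains the strong case: δ = 0.46 − 0.22 = 0.24 and a loss of 0.887 − 0.587 = 0.300 imply γ = −0.300/0.24 = −1.25 SD.

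**4. A second set of assumptions.** Ability L = −0.75·(preterm) + N(0,1); score = 0.8·L + 0.6·N(0,1), so the true difference is 0.8 × 0.75 = 0.60 SD; logit P(follow-up) = −2.2 − aL·L + aG·(preterm). Follow-up has no effect of its own on the score.

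| aL, aG | Passes screen | Difference without → with the rule | Loss against 0.60 |
|---|---|---|---|
| 0.5, 1 | 46% | 0.60 → 0.53 | 12% |
| 1, 0.5 | 78% | 0.60 → 0.48 | 20% |
| 1, 1 | 85% | 0.60 → 0.43 | 28% |
| 1.5, 1 | 97% | 0.60 → 0.32 | 47% |

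Follow-up ran at 31–48% in preterm and 11–17% in control children. A fresh run agreed to within 0.01 on the coefficients and gave power for group falling from 0.59 to between 0.22 and 0.49. With aL = 0 (preterm status only), the same run gave 0.60 → 0.59 for aG = 1 and 0.60 → 0.57 for aG = 2.

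**The case against.** The strongest reply is that the article never says follow-up will be a candidate. It is listed as collected data, and a full candidate list is commonly left to the full protocol or the analysis plan, neither of which is shown. That stands as a reason not to say that follow-up will enter the model. It does not remove the point, because the article states a selection rule, ties it to the group comparison, and leaves the list open. The rule as published admits the variable.

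The second reply is that the cause of follow-up is undocumented. A reader might infer that care is given because of deficits and that the difference is therefore shrunk. The documents do not support this: neuropediatric monitoring or orthoptics could be routine after preterm birth, and the last rows of the first table show a small change or a reversal in that case. This objection stands in full on direction and size.

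Third, the univariate Wilcoxon comparison of the groups uses no covariates and is untouched. This also stands, although the article does not say whether the unadjusted or the adjusted result answers the main objective.

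Two further readings are tempting. One is that allowing follow-up without limit is itself a flaw. No treatment is under test, and a cross-sectional comparison of children under usual care is a legitimate contrast; excluding followed children would select against affected preterm children. The other is that the child's own medication goes unrecorded. The recorded medical history and psychiatric monitoring may cover it, and a condensed article cannot settle what the record form holds.

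**Conclusion.** The point holds in a limited form. The entry rule allows a variable that may be a consequence of the outcome deficit into the model that compares the groups. If follow-up marks the deficit, the adjusted difference can lose from about 4% to nearly half of its size. At the plan's own effect of 0.889 SD the range is 4% to 34%, with power for the group term falling from about 0.91 to between 0.89 and 0.71. If follow-up depends only on preterm status, the loss is at most about 5% without a benefit of care (1 − 0.848/0.889 in the first set; 1 − 0.57/0.60 in the second), and adjustment enlarges the difference when care works.

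These sizes rest on assumed follow-up rates, links and benefits, and on a single binary follow-up variable where the article lists several types. What does not rest on them is that the rule leaves the meaning of the adjusted group coefficient to a data-driven screen. The defect lies in the Statistical Analysis section; the *For the Child* list only supplies the variable.

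**What to change.** In the Statistical Analysis section:

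- keep group in every model that addresses the main objective, whatever its univariate p-value;
- exclude the child follow-up variables listed under *For the Child* from the candidate list of those models;
- state that the contrast is preterm versus full-term under usual follow-up;
- report each type of follow-up by group as number and percentage.

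An analysis that omits followed children is not a substitute, because it conditions on the same variable by restriction and reduces a sample of 28 per group.

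The change takes a few sentences and needs no new data, visits or participants. Its cost is that the adjusted model no longer explores follow-up as a factor; any association with theory of mind can be reported separately and labelled descriptive. The change does not undo a real benefit of care. With an assumed 0.5 SD benefit the unadjusted difference is itself 0.81 or 0.77 SD (moderate or strong link) rather than 0.889, which is why the contrast should be described as one under usual follow-up.

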##### For the Parents

Age, marital status, level of education, occupation, number of children, use of psychoactive substances (alcohol, tobacco, cannabis, etc.), personal and family psychiatric history, and psychiatric/psychological follow-up (psychiatric hospitalization, psychotropic treatments), neurological history (follow-up, treatment).

##### For the Mother

Pregnancy, parity, and miscarriages (number, trimesters, etc.).

#### Sample Size

Because of lack of literature, sample size calculation could not be performed on association between theories of mind and prematurity. Because of link between verbal skills and TOM has been shown in several studies that highlighted the impact of verbal skills on TOM task performance (47, 48), the calculation of the number of subjects required was performed for association between prematurity and WISC VCI with the following hypotheses: an average VCI score for “control” patients of 103.2 ± 12.6 (49) and an average VCI score for “preterm” patients of 92. With an alpha risk of 5%, a power of 90%, and a bilateral test, the number of patients required was 28 per group (NQuery software version 4.0).

#### Data Management

The study will make use of two separated databases for storing research data and contact information. The contact information of patients, such as the participant's name, phone number, and address, will be stored in a separate database unrelated to the research database. In the research database, all participants will receive an ID number. Electronic data will be saved on a secure server with restricted access. In accordance with the national regulations in France, the data will be stored for 15 years after termination of the trial.

#### Statistical Analysis

Descriptive analysis will be performed. Quantitative variables will be expressed as the mean± standard deviation or median (range) and qualitative variables as number (percentage).

Factors associated with development of the affective and cognitive theories of mind separately, notably groups (“preterm”/“full-term”) and parental anxiety, will be studied using univariate analysis (Wilcoxon tests for qualitative variables and Spearman's correlation tests for quantitative variables) and multivariate analysis (linear regression with variables with a *p* < 0.10 by univariate analysis included).

The association between executive functions, evaluated using NEPSY-II, and the development of theories of mind will be studied using univariate analysis (Wilcoxon tests for qualitative variables and Spearman's correlation tests for quantitative variables) and multivariate analysis (linear regression with variables with a *p* < 0.10 by univariate analysis included).

The association between the executive functions, evaluated using the TEA-CH, and the development of the theories of mind will be studied using univariate analysis (Wilcoxon tests for qualitative variables and Spearman's correlation tests for quantitative variables) and multivariate analysis (linear regression with variables with a *p* < 0.10 by univariate analysis included).

A *p* < 0.05 will be considered significant. Statistical analysis will be performed using SAS (Version 9.4, SAS Institute, Cary, NC, USA).

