## Abstract

**Background:** Recent research has identified neuropsychological disorders, specifically executive function disorders, in premature children. Executive functions support goal-oriented mental activity and play a role in the development of social cognition. This underlies the social and emotional behavior of individuals. Parental anxiety is also an important environmental factor that can influence the psycho-emotional development of children.

**Objectives:** The present protocol aims to compare the development of social cognition in school-age children born prematurely to that of school-age children born full-term, and to determine the impact of executive (dys)function and parental anxiety on such development.

**Methods/Design:** In this cross-sectional protocol, 28 prematurely born children aged 7-10 years (“preterm”) and 28 full-term born children aged 7-10 years (“control”) will be included. The “preterm” and “control” groups will be matched for sex and age. The neuropsychological evaluation will include that of non-verbal intellectual efficiency (Raven's colored progressive matrices), verbal level (WISC-IV subtests), and executive functions (NEPSY II subtests and the opposite worlds of TEA-CH). The evaluation of social cognition will be conducted via tests of the theory of cognitive and affective mind. Several dimensions of the level of parental anxiety will be collected through the Spielberg Trait Anxiety Inventory Form Y, Beck Depression Inventory, Social Support Questionnaire-6, Parental Stress Index and, specifically for mothers, the Modified Perinatal Post-Traumatic Stress Disorder Questionnaire.

**Discussion:** The results of this protocol will aid our understanding of the development of social cognition in premature children and to determine the factors that influence such development. This clinical research project, although following a fundamental approach, will have clinical implications because a more precise description of the development of social cognition in this school-age population will make it possible to better determine the cognitive targets of therapeutic actions and to search for predictive indices of the efficacy of practices.

**Trial Registration:**https://clinicaltrials.gov/ct2/show/NCT03007095, identifier: NCT03007095.

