#### Experimental Evaluation of Social Cognition in Exposed and Unexposed Children

Theory of Mind tests are not standardized for the moment, neither in English or French, except for the very simple theory of mind item of the NEPSY-2. Literature on theory of mind is currently based on an experimental approach rather than on a standardized test approach. Our theory of mind assessment is adapted from previous studies. Because of the multiplicity of terms in the field of social cognition – theory of mind implicit, explicit, cognitive, affective- and knowing that it does not cover exactly the same functions, we are interested in what happens between 7 and 10 years old when it comes to articulating the mental states of belief (false belief) or non-intention (false step) to emotions.

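### The groups are matched on sex and age, but the stated analysis does not use the matching, so the group comparison is somewhat conservative if theory-of-mind scores depend on age

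*Protocol article*

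**What the plan says.** The Participants and Procedure for Recruitment section plans 28 preterm and 28 full-term children and states that the "groups will be matched for sex and age (± 3 months"). It does not say whether each preterm child has a named partner or whether the groups are balanced overall.

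The Statistical Analysis section covers group and parental anxiety as factors for each theory-of-mind outcome. It uses "univariate analysis (Wilcoxon tests for qualitative variables and Spearman's correlation tests for quantitative variables"), followed by "linear regression with variables with a *p* < 0.10 by univariate analysis included". No pair, stratum or conditional term is mentioned, and no variable is exempt from the screen. Group, age and sex are all subject to it.

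On the outcome, the section on the experimental evaluation of social cognition says that "Theory of Mind tests are not standardized for the moment". The scores are therefore not said to be age-normed.

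The Sample Size section is based on the WISC verbal comprehension index (VCI): "With an alpha risk of 5%, a power of 90%, and a bilateral test, the number of patients required was 28 per group".

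**The concern.** Matching on age makes the two groups alike in a variable that may drive the outcome. The difference in means then varies less from sample to sample than it would between independent groups. A test that ignores this uses too large a standard error: its true error falls below 5% and power is lost. To collect the benefit, the analysis must contain the matching variables or work on within-pair differences.

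The main objective is the preterm versus full-term comparison of theory of mind, with 28 children per group. A null result could be read as absence of a deficit, so avoidable loss of power matters. The second weakness is the screen. Design variables, and the exposure itself, should not have to earn their place by a p-value, least of all one from a test that the matching has made conservative.

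**Working it through.** **1. The plan's own figure.** Inputs from Sample Size: control mean and SD "patients of 103.2 ± 12.6 (49"), preterm mean "patients of 92", two-sided 5%, power 90%. An SD of 12.6 is assumed for both groups, since only the control SD is given. The difference is 103.2 − 92 = 11.2, so d = 11.2/12.6 = 0.89. The normal approximation gives n = 2(1.960 + 1.282)²/0.889² = 26.6, that is 27 per group. The exact t-test for two independent samples gives power 0.893 at 27 and 0.904 at 28. The stated 28 is thus reproduced as an unpaired design.

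**2. Effect of matching on the unadjusted test.** Let ρ be the within-pair correlation. With close age matching it is roughly the share of variance (R²) explained by age. The unpaired standard error is too large by the factor 1/√(1 − ρ), and the true two-sided error is about 2[1 − Φ(1.96/√(1 − ρ))]:

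- ρ = 0.2: factor 1.118; 1.96/√0.8 = 2.19; error about 2.8%
- ρ = 0.3: factor 1.195; 1.96/√0.7 = 2.34; error about 1.9%
- ρ = 0.4: factor 1.291; 1.96/√0.6 = 2.53; error about 1.1%

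Simulation of the rank-sum test agrees: about 2.6% to 1.1% over this range.

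**3. The whole planned path.** The simulation used 28 pairs, age uniform from 7 to 11 years (up to the eleventh birthday), a partner within 0.25 years, normal errors, no sex effect and 4,000 runs per cell. The screened path lets age in if its Spearman p < 0.10. It counts group as not significant if its rank-sum p ≥ 0.10. The age-score correlation and the 0.6 SD difference are assumptions; the article gives neither. Power (%) at 0.6 SD:

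| Age-score correlation (R²) | Rank-sum | Signed-rank | Screened regression | Age always in | Age passes screen |
|---|---|---|---|---|---|
| 0 (0) | 57.8 | 56.5 | 60.5 | 60.7 | 9% |
| 0.2 (0.04) | 56.6 | 56.8 | 60.0 | 60.9 | 39% |
| 0.3 (0.09) | 56.1 | 58.7 | 62.3 | 63.3 | 68% |
| 0.4 (0.16) | 58.1 | 63.1 | 65.4 | 67.8 | 89% |
| 0.5 (0.25) | 56.8 | 68.1 | 68.3 | 72.4 | 98% |
| 0.6 (0.36) | 57.4 | 75.5 | 72.4 | 79.3 | 100% |
| 0.7 (0.49) | 55.9 | 83.1 | 73.1 | 86.8 | 100% |

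Simulation error is about 0.8 points per cell (√(0.6 × 0.4/4000) = 0.0077).

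Separate runs at R² of 0.2-0.4 gave 57-59% for rank-sum, 65-76% for signed-rank, about 67-72% for the screened path and 70-81% with age always in. The screened path therefore loses about 3-9 points.

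**4. Where the remaining loss arises.** At correlations of 0.6 and 0.7, age enters in every run, yet the screened path still loses 79.3 − 72.4 = 6.9 and 86.8 − 73.1 = 13.7 points. The loss must come from requiring group to pass its own unadjusted screen.

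**5. At the planning effect (d = 0.89).** Screened path against age always in: 92.4 v 93.0 at correlation 0.3, 95.5 v 96.3 at 0.5, 97.2 v 98.3 at 0.6 and 98.1 v 99.7 at 0.7. The loss is about 1 point, at most 1.6.

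**The case against.** A reader might infer that the plan gives up some 18 points of power, by setting a rank-sum test at 57% against age-adjusted regression at 75% (R² = 0.3, 0.6 SD). The documents do not support that contrast. The plan goes on to a regression, age is a candidate for it, and at R² of 0.2-0.4 age passes the screen in 95-100% of runs. Part of the gap is also not about matching: with no age effect at all, regression already beats the rank-sum test by about 3 points (60.8% without age, against 57.8%).

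Other strong readings also fail. Individual pairing is likely, because a 3-month tolerance suggests closeness to a particular partner, but it is not stated; under frequency matching no signed-rank test would be available. The form of the Wilcoxon test is not named. The rank-sum form is inferred from its use for all qualitative factors and from the unpaired sample size. No confidence interval is planned, so it cannot be said that a planned interval is too wide. That the tests are not standardised makes an age effect plausible but does not give its size. The signed-rank test is not always better: with no age effect it is slightly weaker (56.5% v 57.8%).

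These points stand, and they reduce the size of the problem. They do not remove it. The article states an entry rule with no exception for group, age or sex, and that rule is wrong for a matched design. A condensed article may leave detail to a fuller plan, but this rule is stated outright.

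**Conclusion.** The point holds as a modest loss of efficiency. As described, the analysis does not respect the matching, and the main comparison has to pass a conservative unadjusted test before it can enter the model. At a true difference of 0.6 SD, the full planned path loses about 3-9 points of power if age explains 20-40% of the score variance and about 1 point at R² of 0.04-0.09. At 0.89 SD it loses about 1 point. Without an age effect it loses nothing. The univariate test read alone loses more.

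These sizes rest on an assumed age effect, an assumed 0.6 SD difference and close individual matching. The 0.89 SD effect belongs to the VCI; the article says that no calculation could be made for theory of mind, so a smaller effect cannot be ruled out. The error is in the conservative direction and does not raise the false-positive rate. The change should be made because it is nearly free, not because the main conclusion would otherwise be invalid.

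**What to change.** For the main objective, regress each theory-of-mind score on group, with age (continuous) and sex always in the model and group kept in regardless of the p < 0.10 screen. Report this as the main group comparison.

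State whether matching is by individual pair or by group frequency. If by pair, keep pair identifiers in the research database and use the signed-rank test on within-pair differences as the rank-based check, in place of the rank-sum test for group.

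The cost is a change of wording and about two degrees of freedom, with a negligible loss of power for the signed-rank test if age turns out to be unrelated to the score. Age and sex are already collected; no further children or visits are needed.
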